### Data collection, management, and quality assurance

Enumerators will enter data on tablet-based questionnaires created using Research Electronic Data Capture (REDCap) [27,28]. REDCap is a secure, cloud-based software platform designed to support data capture for research studies. A new form will be created for each respondent, and forms will be submitted immediately upon completion of the interview. Paper surveys will be available but will only be used in the event of technology failure. All enumerators will be accompanied by a team leader to ensure accuracy. The survey is in English and will be translated into Dholuo, the most commonly spoken language in this population. Enumerators will use the translation version preferred by the respondent. The intent of each question will be established with enumerators during training prior to administration.

Risk of information sharing will be minimized through a password-protected tablet and mobile platform account with restricted device access. The data will be stored offline on the tablet application until synced to an online, privacy-protected server. All data will be uploaded to the online server for initial analysis through REDCap. Data quality checks will be conducted daily (Fig 3). Feedback from any data discrepancies will be shared with enumerators to maintain high-quality data entry. All variables will be checked line-by-line for any outliers. Surveys will be checked for internal validity, including checking for consistent answers regarding sex and household population. Surveys will also be checked for completeness and any missing data. Discrepancies in data will be resolved by the Data Management Team in conjunction with the enumerators involved. Any changes will be made through REDCap data management tools.

**Fig 3 pone.0256555.g003:**
[figure not shown]
Data quality plan. Daily, bidirectional data quality checks will be conducted to ensure high-quality data collection. Enumerators will log any quality concerns and any issues during the survey day, which are reported to Team Leaders. Team Leaders review these forms and report to the Supervisor. The Supervisor then creates an aggregate summary that is distributed to the Data Management Team at the end of each survey day. The Data Management Team reviews the data present in REDCap each night for both internal validity and accuracy compared to field reports. This then forms the basis of a quality report that is reviewed with Supervisors and Team Leaders prior to the next survey day.

Raw data will be stored centrally in the REDCap online platform. At the conclusion of each survey round, raw data will be exported to Stata for data cleaning and processing. Data cleaning will be completed by the Data Management Team, and detailed records of all changes will be kept. A final, clean dataset will be kept in a central, password-protected location. All analyses will be conducted using this cleaned dataset.

### Data analysis

After administration, data will be exported to the latest version of Stata (StataCorp LP, College Station, TX) for further analysis. Initial analyses will focus on descriptive statistics of health, socioeconomic, and education metrics in the sample population across areas. Further analyses will characterize these metrics in terms of demographic variables and compare these metrics to county and national averages using appropriate statistical tests, including chi-squared tests, t-tests, ANOVA, and non-parametric tests. These analyses will be conducted following each survey in 2021, 2024, and 2027.

Analysis of outcome metrics will be conducted using multivariable linear regression, logistic regression, and generalized estimating equations. Specific primary outcomes of interest include under-five mortality, immunization rate, skilled delivery rate, contraceptive prevalence rate, and antenatal care visits. Longitudinal analyses will be performed at the end of the study in 2027 once multiple timepoints are available. Interim longitudinal analyses will also be performed following each survey administration. Trends in outcomes and potential effects of programs will be assessed. This will involve interrupted time series techniques with a segmented regression to asses intervention effects over repeated observations.

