### Sample size

The study has a wide range of indicators of interest, including child mortality, skilled delivery rate, vaccination coverage, contraceptive prevalence, and antenatal care. These metrics vary in their community prevalence and would thus require different sample sizes. For example, under-five mortality is relatively rare at 82 per 1,000 live births while full vaccination is relatively common at 57.2% of children [1]. A community prevalence of 50%, yielding maximum variation and therefore maximum sample size, was used to adequately power all metrics. Within each area, the sample size was calculated to detect a 10% difference over time using a power of 80%, precision of 0.05, and design effect of 1.6. Design effect was calculated according to the equation:
DE=(1+(m−1))*ICC
where DE is the design effect, m is the number of the household to be sampled per cluster, and ICC is the inter-cluster correlation. An ICC of 0.15 was used based on international standards [9]. This would require a sample of 621 households in each area. This estimate was inflated by 30% to give a total goal sample of 887 per area. For the first survey, which includes eight areas, the total sample size will be 7,096 households. Subsequent surveys will include the same number of households per area. Table 2 below shows the sample size for each ward.

**Table 2 pone.0256555.t002:** Sample sizes for successive surveys.

	Minimum	Maximum	Number of clusters	Households with children	Additional Households	Total per Cluster
North Kamagambo	621	887	127	5	2	7
East Kamagambo	621	887	127	5	2	7
Central Kamagambo	621	887	127	5	2	7
South Kamagambo	621	887	127	5	2	7
North Sakwa	621	887	127	5	2	7
Central Sakwa	621	887	127	5	2	7
Central Kanyamkago	621	887	127	5	2	7
West Kanyamkago	621	887	127	5	2	7

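### The survey is sized for clustering within grid cells, but the tests and regressions in the analysis section are not said to account for it

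*Protocol article*

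**What the plan says.** Under Sample size, the protocol article states, for every ward alike, that "the sample size was calculated to detect a 10% difference over time using a power of 80%, precision of 0.05, and design effect of 1.6", and that "An ICC of 0.15 was used based on international standards". The result is 621 households per area, raised to 887. Under Sampling strategy, each area is divided into 127 grid squares. A team starts at the centre of each square and surveys houses along one random direction until it has seven households, at least five of them with a child under five.

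Under Data analysis, the work across areas is first described as descriptive. Metrics are then broken down by demographic variables and set against county and national averages "using appropriate statistical tests, including chi-squared tests, t-tests, ANOVA, and non-parametric tests". These analyses are to be repeated after the 2021, 2024 and 2027 surveys. Outcome metrics are assigned to multivariable linear regression, logistic regression and generalized estimating equations (GEE), and programme effects to segmented regression. The section names no cluster unit, design-based variance or robust standard error for any of these methods.

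**The concern.** Chi-squared tests, t-tests, ANOVA and the usual rank tests treat households as independent, and so do linear and logistic regression with default standard errors. The sample size section assumes that they are not: it raises the requirement by 60% because neighbouring households resemble each other. If the analysis ignores what the sizing allowed for, standard errors are too small wherever the contrast does not vary within a cell. Two kinds of planned analysis are exposed:

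- the comparison of an area's metric with a county or national figure;
- a regression coefficient for something that is constant within a cell, such as ward or programme status.

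At stake is an excess of apparent departures from the county or national level, and intervals that claim more precision than the design delivers. Listing GEE protects the outcome analyses only if the grid cell, or a larger unit that contains it, is the GEE cluster. The section does not say so.

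**Working it through.** **Inputs, all from the Sample size and Sampling strategy sections:** prevalence 50%, difference 10 percentage points, power 80%, alpha 0.05 (called precision there; two-sided reproduces the stated figure), ICC 0.15, design effect (DE) 1.6, 127 cells per area, 7 households per cell of which at least 5 have a young child.

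**1. The plan's own figure.** Two proportions, 0.50 against 0.60, without continuity correction:

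n = [1.960 × √(2 × 0.55 × 0.45) + 0.842 × √(0.25 + 0.24)]² / 0.10² = 387.3, so 388.

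388 × 1.6 = 620.8, so 621. Then 621 / 0.70 = 887.1 (stated as 887), and 8 × 887 = 7,096. The stated sample size reproduces, so clustering is built into it.

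**2. Design effect.** The standard form is DE = 1 + (m − 1) × ICC.

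- m = 5: 1 + 4 × 0.15 = 1.6, the value used.
- m = 7: 1 + 6 × 0.15 = 1.9, for all households in a cell.

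The formula as printed has its bracket misplaced: it would give 0.75 at m = 5 and 1.05 at m = 7. The value of 1.6 comes from the standard form.

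**3. True size of an unadjusted 1-df test at nominal 5%,** for an area against a reference treated as fixed: 2 × [1 − Φ(1.96 / √DE)].

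- DE 1.6: 1.96 / 1.265 = 1.55, giving 12.1%.
- DE 1.9: 1.96 / 1.378 = 1.42, giving 15.5%.

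**4. Interval width.** An unadjusted interval is too narrow by 1 − 1/√DE: 21% at DE 1.6 and 27% at DE 1.9.

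**5. Check by simulation.** Beta-binomial data with 127 cells per group, ICC 0.15, prevalence 50% and 6,000 runs. The same formula applies to two groups made of whole cells.

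| Contrast | 5 per cell | 7 per cell |
|---|---|---|
| Between groups of whole cells | 12.6% | 15.5% |
| Covariate varying freely within cells | 5.1% | 5.0% |

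The inflation belongs to contrasts that are constant within a cell. It is absent for a demographic variable that varies at random within cells.

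**6. Sensitivity to the ICC,** same formula as step 3. The ICC values below 0.15 are assumptions, because the article gives one planning value for all metrics.

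| ICC | 5 per cell | 7 per cell |
|---|---|---|
| 0.02 | 5.9% | 6.4% |
| 0.05 | 7.4% | 8.6% |
| 0.10 | 9.8% | 12.1% |
| 0.15 | 12.1% | 15.5% |

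**The case against.** **The article does not say that the tests are unadjusted.** It calls them appropriate and leaves the list open. Design-adjusted versions of the same tests exist, and a condensed article may leave variance estimation to the full plan. This stands to the extent that a reader who infers a commitment to ordinary tests goes beyond the text. It does not remove the point: the sentence goes on to name tests whose standard form conflicts with the article's own ICC, and nothing elsewhere in the section corrects it.

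**The named tests are not assigned to comparisons between areas.** This stands. The sentence covers demographic breakdowns and county or national averages, and work across areas in that paragraph is descriptive. An unadjusted 7-df test across the eight areas would have 26.8% (DE 1.6) to 38.8% (DE 1.9) false positives, but the article does not plan one there, so that figure should not be charged to it.

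**Every cell is visited.** This is the strongest technical objection. Each area is split into 127 squares and Table 2 lists 127 clusters, so for a ward's own prevalence the cells behave partly like strata. If households were drawn at random within equal-sized cells, between-cell variance would drop out. The design effect would then be about 1 − 0.15 = 0.85, and an unadjusted test would have a true size of about 3.4%, on the conservative side. But households are taken along one line from one starting point, not at random within the cell, so neighbourhood similarity along the line still enters the sampling error by an unknown amount. The objection makes the actual design effect uncertain. It does not show that clustering can be ignored.

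**These are secondary, descriptive tests.** This is largely true, and it lowers the severity. A reader might also infer that these p-values go to policy makers after every round. The Results dissemination section names policy makers as an audience but does not say that.

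**Conclusion.** The mismatch is real: the sizing allows for clustering within cells, and the analysis section does not carry it into the tests or the regressions. The size of the problem is conditional. About 12% to 16% false positives, with intervals 21% to 27% too narrow, applies if the methods are run in standard form, if the contrast has 1 df and is constant within a cell or is made against a fixed reference, and if the ICC is 0.15 with cells acting as sampled clusters.

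It would be tempting to read 12% to 16% as the error rate of the plan as a whole. The documents do not support that: contrasts that vary freely within cells stay near 5%, a lower ICC shrinks the effect, and full coverage of the cells leaves the true design effect open. Nor do they support a claim that the outcome analyses are invalid, since GEE is listed and only its cluster unit is missing. Treating the cell as the sampling unit is the conservative choice and the one consistent with the sizing. Severity: should-fix.

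**What to change.** Add to Data analysis a statement that every test and model accounts for the sampling design, with the grid cell as cluster and the ward as stratum. Specifically:

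- Rao-Scott chi-squared tests in place of standard chi-squared tests;
- design-adjusted Wald or F tests in place of t-tests and ANOVA, and a design-based counterpart for any rank test;
- cell-clustered standard errors for linear and logistic models;
- the grid cell named as the GEE cluster.

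Add one line saying that all cells of an area are visited and that treating them as sampled clusters is a deliberate, conservative choice.

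The cost is a few sentences and a survey declaration in Stata, with no new data and no change in sample size. Intervals for the affected contrasts widen: by 26% at DE 1.6 (√1.6 = 1.265) and 38% at DE 1.9 (√1.9 = 1.378) relative to unadjusted ones, if the planning ICC is right, and by less if it is too high. If adjustment is already intended, the statement simply records it.

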**Fig 2 pone.0256555.g002:**
[figure not shown]
Lwala Community Alliance theory of change. Lwala utilizes a community-led model to improve health, education, and economic outcomes.

Lwala’s efforts in North Kamagambo have led to significant successes in several key health metrics, including being on track to outpace Millennium and Sustainable Development Goal (SDG) targets for childhood mortality, attaining an under-five mortality rate of 29.5 per 1,000 live births as of 2017 [3] compared to the SDG target of under 25 deaths per 1,000 live births by 2030 [4]. This success has led to local health authorities inviting Lwala to expand its CHW model into nearby East and South Kamagambo wards, as well as to begin providing technical assistance toward improved health service delivery in the government-supported health facilities of these wards. Along with service expansion has come the effort to systematically and academically evaluate health metrics and changes in outcomes in the community. This led to multiple iterations of a community-wide household survey in Lwala’s original catchment area and subsequently in the expansion areas [3,5,6]. We now aim to conduct repeated cross-sectional surveys to evaluate the effect of Lwala’s programming over time and characterize health metrics in the area.

Here we describe the Lwala Household Survey (LHS) with the following objectives: (1) to assess the health, socioeconomic, and education status of current and future communities receiving programming from Lwala; (2) to measure changes in these metrics over time in the presence of Lwala programming; (3) to compare changes over time in key metrics to determine the effect of Lwala presence and programming.

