### Study population, setting, and timeline

Located in the Lake Victoria region of southwestern Kenya, Migori county had a population of 1.1 million people during the 2019 National Census [7]. Administratively, there are 10 sub-counties, each with multiple smaller electoral sub-divisions called wards [8]. With an average household size of 4.6 and a growth rate of 3.1%, it is highly densely populated (427 persons per square kilometer) [7,8]. About 90% of the population live in rural areas, largely in mud-walled houses with agriculture and fishing as the main livelihoods [8].

Lwala programming began in North Kamagambo, an area covering 46.4 square kilometers, in Rongo, which is one of the 10 sub-counties, in 2007 (Fig 1). Programs were subsequently expanded to other wards in Rongo, namely East Kamagambo in 2018 and South Kamagambo in 2019. Programming will be expanded to Central Kamagambo within Rongo in 2021 following the first survey administration. Lwala’s area of programming is expanding approximately every two years, with the next round of expansions planned for Awendo sub-county. The first iteration of this survey in 2021 will be administered in current programming wards in Rongo sub-county (North Kamagambo, East Kamagambo, South Kamagambo) and the future programming ward in Rongo sub-county (Central Kamagambo). It will also include two representative wards in Awendo sub-county (North Sakwa and Central Sakwa).

The initial survey will also include two comparison wards in Uriri sub-county (Central Kanyamkago and West Kanyamkago). Uriri sub-county is adjacent enough to be a comparable location but distant enough to minimize spillover effects. In addition, Uriri sub-county has a similar socio-economic and demographic context that is analogous to Rongo sub-County. Within Uriri sub-County, Central Kanyamkago was selected as a peri-urban ward to serve as a comparison with the peri-urban Central Kamagambo. Similarly, West Kanyamkago was selected as a rural ward to compare with more rural programming wards. While Uriri has government health facilities that are typical of Migori County, there is no similar organization to Lwala.

All subsequent surveys (2024 and 2027) will include the areas from the initial 2021 survey (Table 1). Any further expansion areas that are identified will also be included. Inclusion of new wards will be approved by the investigators with subsequent amendments made to Institutional Review Board protocols.

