### Sampling strategy

Households will be selected using a hybrid sampling technique to obtain as random of a sample as is feasible. Because a truly random sample would be logistically infeasible due to expense and lack of a household-level sampling frame, a hybrid systematic and random sampling technique will be used. To accomplish this, a modified procedure based on the World Health Organization Expanded Programme of Immunization (EPI) method will be used [10,11]. First, each area will be split into 127 grid squares using Geographic Information System (GIS) technology. The center point of each grid cell will then be generated using GIS. This is the starting location for the enumerators for each day’s survey. GPS will be used to navigate to the precise starting location each morning.

After arrival at the center point, the spin-the-bottle technique will be used [10]. Each enumerator team will be supplied with a random direction by spinning a pen or bottle. On arrival to the center of the grid cell, they will travel in the given direction surveying houses along the line given by the direction.

As many of Lwala’s programs and outcomes of interest focus around maternal and child health, households with children under five years of age will be oversampled. At least five of seven surveys administered in each grid square will be administered to households with children under five years. If the enumerator reaches the end of the grid cell before surveying both seven total households and five households with a child under five years, they will walk along the edge of the grid to the closest corner to find more households.

This approach minimizes the biases of the traditional spin-the-bottle sampling method [12] by using the center of an arbitrary square in place of the center of a town or gathering area.

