## Discussion

### Limitations

Intrinsic to survey research is the use of self-reported data. Some of the survey questions employ direct observation, but the large majority of questions require the participant to recall information and offer sensitive opinions about themselves. We have minimized this limitation to the extent possible by using validated questions that include prompts and training enumerators in making participants comfortable. The cross-sectional nature of the survey makes determining causal relationships difficult. The use of repeated cross-sectional surveys and sophisticated statistical methods will allow some commentary on causation, but the study will not have the same power as a randomized trial. However, randomization is not feasible given the unpredictable nature of expansion wards, which are chosen based on policy, organizational, and financial factors. Further, many of the quasi-experimental methods of program evaluation rely on the parallel trends assumption to create the counter-factual. While this study has a comparison group in the areas in Uriri, there is a single pre-implementation data point available for most intervention areas. This makes evaluation of the parallel trends assumption difficult. Finally, the repeated cross-sectional design loses power by not collecting longitudinal data for the same households over time. However, it was not logistically feasible to visit the same households at each timepoint. Phone numbers will be collected, and further studies will follow smaller sets of outcomes over time within households.

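### Programme-effect inference rests on eight wards, two of them comparison wards in one sub-county, and the named methods make no allowance for so few allocated units

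*Protocol article*

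**What the plan says.** The third objective in the Introduction is "to compare changes over time in key metrics to determine the effect of Lwala presence and programming". The Data analysis section states: "Analysis of outcome metrics will be conducted using multivariable linear regression, logistic regression, and generalized estimating equations". On trends and programme effects it adds: "This will involve interrupted time series techniques with a segmented regression to asses intervention effects over repeated observations". It names no unit of independence and no correction for a small number of units.

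The Sample size section gives the number of areas: "For the first survey, which includes eight areas, the total sample size will be 7,096 households". The timeline section describes "two comparison wards in Uriri sub-county". Table 1 gives programme starts of 2007, 2018, 2019 and 2021 for the four Rongo wards and 2022 for the two Awendo wards. Allocation is by ward and not random; the Limitations section says "randomization is not feasible given the unpredictable nature of expansion wards, which are chosen based on policy, organizational, and financial factors". Below ward level, "First, each area will be split into 127 grid squares using Geographic Information System (GIS) technology", with seven households per cell (Table 2).

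The Limitations section covers non-randomisation, the single pre-implementation round in most intervention areas and the difficulty of checking parallel trends. It does not mention the number of wards.

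**The concern.** About 7,000 households per round looks like ample data, but for objective 3 the unit that receives or does not receive the programme is the ward. A drought, a staffing change or a county campaign that moves a whole ward cannot be told apart from the programme by interviewing more households in that ward. Segmented regression does not remove the problem: it specifies the mean, and its standard errors still depend on what is treated as independent.

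There are two natural choices. Clustering on wards leaves very few clusters, with two in the comparison group, and the usual robust variance is then biased downward. Clustering on grid cells gives over a thousand clusters but assumes that wards do not drift apart for reasons other than the programme. In either case intervals can be too narrow, and chance divergence between Uriri and the programme wards could be reported as a programme effect.

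**Working it through.** **The plan's own figure.** Two proportions, 50% v 60%, two-sided 5%, 80% power: 388 per survey. 388 × 1.6 = 620.8, so 621. 621 / 0.70 = 887. 887 × 8 = 7,096. The figures reproduce. They concern change within one area and contain no ward-level variance.

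**Inputs.** Prevalence 0.5 and ICC 0.15 (Sample size); 127 cells of 7 = 889 households per ward and round (Table 2). With 7 households per cell, 1 + (7 − 1) × 0.15 = 1.9. (The stated 1.6 corresponds to 5 per cell.) The SD s of true ward changes is not in the document. It is assumed to be 0, 2, 3 or 5 percentage points.

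**Variance of one ward's change between two rounds.** Sampling part, taking rounds as independent: 2 × 0.25 × 1.9 / 889 = 0.001069. Total: 0.001069 + s².

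**Clustered by ward, uncorrected.** With a programme and b comparison wards, the expected robust variance is proportional to (a − 1)/a² + (b − 1)/b², against a true 1/a + 1/b.

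- 6 v 2: (5/36 + 1/4) / (1/6 + 1/2) = 0.389 / 0.667 = 0.58.
- 3 v 2: (2/9 + 1/4) / (1/3 + 1/2) = 0.472 / 0.833 = 0.57.

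The variance is understated by over 40% whatever s is. Simulated rejection under a true null:

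| Contrast | z test |
|---|---|
| 6 v 2 ward changes | 23% (21% with the factor 8/7) |
| 3 v 2 ward changes | 24% (20% with the factor 5/4) |
| All Table 1 rounds, ward and round effects | 11-14% |

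A t reference with wards minus 1 degrees of freedom still gives about 14%, 11% and 6-8% respectively. A check with logistic GEE on binary data, with only 169-246 runs per setting, gave 21-27% for the 6 v 2 cross-section and the 3 v 2 change.

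**Clustered by grid cell.** The test sees only the sampling part, so rejection is 2 × P(Z > 1.96 × √(0.001069 / (0.001069 + s²))).

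| s (points) | √ ratio | Rejection |
|---|---|---|
| 0 | 1.000 | 5% |
| 2 | 0.853 | 9% |
| 3 | 0.737 | 15% |
| 5 | 0.547 | 28% |

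**Which wards change status.** From the 2021 round onward, Table 1 shows three: Central Kamagambo (programme after the 2021 survey), North Sakwa and Central Sakwa (2022). North Kamagambo (2007) and East Kamagambo (2018) have no round before their start. South Kamagambo's first round falls in its start year, 2019. The newly served contrast is therefore about 3 v 2, with 3 + 2 − 2 = 3 degrees of freedom.

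**Ward-level t test, 3 v 2.** SE = √((0.001069 + s²) × 5/6), critical value 3.182. The test holds 5% when ward changes are independent with equal variance. Power for a 10-point effect:

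| s (points) | SE | 0.10 / SE | Power |
|---|---|---|---|
| 0 | 0.0298 | 3.35 | 62% |
| 2 | 0.0350 | 2.86 | 50% |
| 3 | 0.0405 | 2.47 | 40% |
| 5 | 0.0545 | 1.83 | 25% |

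A permutation test is no way out for 3 v 2. There are 10 ways to choose the two comparison wards from five, so the smallest p-value is 1/10.

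**The case against.** The strongest reply is that the article does not commit to the faulty analysis. It names model families, not a clustering unit, a robust variance or a normal reference. A ward-clustered GEE with a small-sample correction fits its wording, and a statistical analysis plan that is not shown may specify one. This stands against any claim that an invalid test has been prescribed. It does not remove the point, because the scarcity of wards is fixed by the design and no analysis plan can add comparison wards. The limitations discuss the comparison group without mentioning its size.

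A reader might infer that standard errors are too small whichever level is used for clustering. The document does not support that. With no ward-level variation in change, cell-clustered tests hold 5%, and the document gives no ward variance. Identical change in eight wards across three sub-counties, some peri-urban and some rural, is a strong thing to rely on, but the over-rejection remains conditional.

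A reader might also infer that programme effects rest on GEE alone. They do not: GEE is listed for outcome metrics in general, and segmented regression is the method tied to intervention effects.

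Finally, the design is not a simple 6 v 2 comparison of change. This objection stands in full and shapes the remedy. The article's caution on causation and parallel trends is also fair, but it concerns bias, not the precision available from so few wards.

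**Conclusion.** The point holds in a limited form. Objective 3 depends on eight wards with two comparison wards in one sub-county, and the article neither allows for this in the named methods nor discloses it as a limit.

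Without a correction, ward clustering rejects about 11-25% of true nulls. This result needs no assumption about ward variance, but it does assume an uncorrected robust z test. Cell clustering rejects about 9%, 15% and 28% at ward-change SDs of 2, 3 and 5 points, and 5% at zero; those SDs are assumed.

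Two further limits apply. The calculations use a 50% outcome, so rarer outcomes such as under-five mortality will differ. And even a ward-level test treats the two Uriri wards as independent; a change common to that sub-county would undermine it, and the design cannot separate such a change from a programme effect.

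**What to change.** For every programme-effect estimate, including the segmented regression, code exposure by each ward's start date in Table 1 and include ward and round effects. Base inference on wards, either by clustered models with a small-sample correction or by a ward-level summary. Its degrees of freedom should match the wards that change status: about 3 v 2 wards and 3 degrees of freedom from the 2021 baseline.

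Do not substitute a t test on eight ward changes with 6 degrees of freedom. If the three already-served wards are assumed to change no further, a 10-point effect in the three new wards averages to (3 × 10 + 3 × 0) / 6 = 5 points, and power falls to 3-6%.

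Keep cell-clustered intervals for ward-specific estimates. Add to the limitations that two comparison wards in one sub-county restrict inference on the programme effect, and give the expected power.

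The change costs some wording and a little code. The downside is wider intervals and the low power shown above, below 80% even with no ward-level variation.
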